## Methods/Design

### Overview and hypotheses

Pregnant women or new mothers within one month of delivery who reside in one of six urban neighborhoods in Hartford, CT and were recruited into the NFN program were invited to participate in ECHO. These six neighborhoods were chosen because they are served by a Brighter Future Family (BFF) Center that is linked to the Nurturing Families Network home visitation program. Brighter Future Family Centers provide early childhood education programs and parenting classes designed to improve parents’ knowledge of child development and nurturing skills, support in earning a high school degree, understanding and speaking English, computer use and financial literacy and family play groups. Centers also provide information to parents about other community, city, state and national resources that might help them.

The six Brighter Future Family (BFF) Centers in Hartford, Connecticut and their NFN programs were paired by neighborhood socioeconomic and racial/ethnic characteristics (Table 1) and were randomly assigned to receive either the standard NFN home visitation program (n = 3) or the enhanced NFN home visitation program (NFN+, n = 3). The goal was to recruit 60 mothers and their newborns (10 from each BFF Center and its corresponding neighborhood) for a total of 30 mother/newborn dyads from an intervention BFF Center and its neighborhood and 30 dyads from a control BFF Center and its neighborhood. All dyads received the standard NFN curriculum using PAT and Partners curricula with weekly home visits. In addition, the NFN+ dyads received an enhanced curriculum in the areas of goal-setting, problem-solving, stimulus control and skill-building related to nutrition, physical activity, cues, and routines as well as enhanced neighborhood community services including coupons for Farmer’s Markets and grocery stores, cooking classes, and exercise classes.

**Table 1 Tab1:** Demographics of neighborhood pairs selected for randomization^a^

Neighborhood pair	1	2	3
Average family income	$28,191	$46,730	$33,697
Poverty rate^b^	42 %	14 %	34 %
Number of births (2010)	466	222	311
Total population (2010)	19,655	20,308	15,512
% Hispanic	50 %	32 %	41 %
% Black	32 %	45 %	44 %

^a^
http://www.hartfordinfo.org/Snapshots/neighborhood. Last accessed May 10, 2015

^b^City of Hartford Department of Health and Human Services. *A Community Health Needs Assessment.* Hartford, CT: City of Hartford Department of Health and Human Services;2012

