### Participants

Women who were either prenatal or had just delivered a baby were screened for eligibility for the NFN program using the Revised Early Identification Screening Tool (Reid). The Reid screen consists of 17 items including poverty, unemployment, single head of household, substance abuse, psychiatric care or late prenatal care with a positive Reid screen score being 3 or more affirmative responses. Final eligibility for the NFN Home Visitation Program was determined using results from the Kempe Family Scale which was administered during the first home visit [47, 48] by the NFN Supervisor. Prenatal women enrolled in NFN were further screened for eligibility in ECHO; final determination of eligibility occurred after the birth of the infant. Inclusion criteria for ECHO included singleton birth greater than 34 weeks gestation, any maternal race or ethnicity, no chronic conditions that could affect the growth or development of the infant and residence at the time of the infant’s birth in an ECHO-designated neighborhood. Infants with major malformations, admission to the neonatal intensive care unit or a prolonged hospital stay or infants who were small for gestational age and required special or supplemental nutrition were excluded.

Between November 2013 and December 2014, 117 mothers were screened for enrollment in ECHO and 57 met all initial eligibility criteria, provided consent, and were randomized into either the intervention (n = 30) or control (n = 27) arms (Fig. 2). After the birth of their newborn, 49 dyads continued to meet all final eligibility criteria. Of the 8 dyads that dropped out after providing consent, 2 left the NFN program prenatally, 4 had infants who did not meet eligibility criteria, 1 mother moved out of the area prenatally and 1 mother had special needs that precluded her participation in the study. The demographics of the 49 maternal-infant dyads that met all eligibility criteria are shown in Table 2.

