#### Sample size, power calculation

This is an initial efficacy trial that is constrained by the size of the budget. However, 60 participants with a 20 % drop out rate is sufficient to detect a decrease of approximately 0.3 in the proportion of children under 6 months of age receiving SSB/juice and/or solid food with a power of 80 % and an alpha = 0.05.

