### Statistical analysis plan for primary outcomes

The primary outcome measure is the duration and exclusivity of breastfeeding, the time to consumption of SSB/juice and solids, the amount of television/screen time per day, and sleep duration in NFN+ infants as compared to NFN infants. The quality of the randomization and the comparability of the participants have been assessed using >Chi square and t-tests as appropriate (Table 2). Participants were comparable except that intervention participants had higher parity as compared to control participants. Participants are nested and clustered within neighborhoods and these effects are being evaluated and will be controlled for in the statistical analysis. Using an intention to treat and a per protocol analysis, behaviors of NFN+ mothers will be compared to NFN mothers related to SSB/juice consumption (number of ounces per day, age at introduction of SSB/juice; age at beginning solids, duration (weeks) of breastfeeding and sleep duration, soothability, and television viewing hours) using two sample t-tests or Wilcoxon tests. Chi square analysis will be used to compare the proportions of exclusive breastfeeding at 6 months in the two groups. Similarly, we will determine if the intervention decreases the risk that infants would stop exclusive breastfeeding at any time considered in the study. A p ≤ 0.05 will be considered significant.

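### The plan promises to control for clustering but names individual-level t, Wilcoxon and chi-square tests, although six paired centres were randomised 3 vs 3

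*Protocol article*

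**What the plan says.** **Design.** Protocol article, Overview and hypotheses: the six centres and their home visitation programmes "were paired by neighborhood socioeconomic and racial/ethnic characteristics" and were then randomly assigned, three to the standard and three to the enhanced programme. The Methods/Design part of the Abstract agrees that centres were randomised. The target was to "recruit 60 mothers and their newborns (10 from each BFF Center and its corresponding neighborhood". The Participants section words it differently and says of the 57 consenting mothers that they "were randomized into either the intervention" or the control arm.

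**Analysis.** Statistical analysis plan for primary outcomes: "Participants are nested and clustered within neighborhoods and these effects are being evaluated and will be controlled for in the statistical analysis". The same paragraph then sets out the comparisons of NFN+ with NFN mothers:
- SSB/juice intake, age at first SSB/juice and at first solids, breastfeeding duration, sleep duration, soothability and television hours are compared "using two sample t-tests or Wilcoxon tests".
- The proportions exclusively breastfed at 6 months are compared by chi-square.
- The risk of stopping exclusive breastfeeding at any time is also to be examined; no test is named for it.

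Significance is p ≤ 0.05. The section on secondary outcomes analyses fruit and vegetable consumption and centre use in the same way as the primary hypotheses, and weight-for-length categories by chi-square. The analysis sections name no mixed model, GEE, centre-level summary or pair term.

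**The concern.** What was randomised is the centre, and there are six of them. Infants of one centre share home visitors, local programmes and stores, and a neighbourhood, so their outcomes may be correlated. A t, Wilcoxon or chi-square test on individual mothers or infants treats them as independent, and chance differences between the three centres of one arm and the three of the other can then pass for an intervention effect.

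The paragraph recognises the nesting and promises to deal with it, but the tests it names, applied as worded, cannot keep that promise. Two analysts could both claim to follow the plan and reach different p-values, one on about 46 degrees of freedom and one on 4 or 2. At stake is whether the stated 0.05 level holds for the outcomes on which efficacy will be judged.

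**Working it through.** **Inputs from the document**
- Randomised units: 6 centres, 3 vs 3, in 3 pairs (Overview and hypotheses).
- Centre size: 60 × 0.80 / 6 = 8 after the assumed 20 % drop-out (Sample size, power calculation). The 49 dyads finally eligible (Participants) give 49 / 6 = 8.2. So m = 8, or 24 per arm.
- Significance level: 0.05 (primary analysis section).

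**Assumed inputs.** The document gives no ICC; 0.01 to 0.10 is taken as a range. The share *s* of between-centre variance removed by pairing is not given either; 0, one half and 1 are shown.

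**Step 1: the plan's own figure.** With ICC = 0, 40,000 simulated trials of 3 vs 3 centres of 8 and no true effect give a t-test rejection rate of 0.0496. The nominal 0.05 is reproduced when there is no clustering. (The 80 % power statement is a separate matter and nothing here rests on it.)

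**Step 2: formula.** Relative to independent infants, the variance of the difference between arms is multiplied by

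F = 1 + [m(1 − s) − 1] × ICC

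With s = 0 this is the usual design effect 1 + (m − 1) × ICC. The approximate true two-sided error of the unadjusted test is 2 × [1 − Φ(1.96 / √F)].

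Worked example, s = 0, ICC = 0.10: F = 1 + 7 × 0.10 = 1.70; √F = 1.304; 1.96 / 1.304 = 1.503; error = 0.133.

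| ICC (assumed) | Share removed by pairing | F | Error, formula | Error, simulated t-test |
|---|---|---|---|---|
| 0.01 | none | 1.07 | 0.058 | 0.057 |
| 0.02 | none | 1.14 | 0.066 | 0.063 |
| 0.05 | none | 1.35 | 0.092 | 0.094 |
| 0.10 | none | 1.70 | 0.133 | 0.133 |
| 0.05 | half | 1.15 | 0.068 | 0.069 |
| 0.10 | half | 1.30 | 0.086 | 0.089 |
| 0.05 | all | 0.95 | 0.044 | 0.045 |
| 0.10 | all | 0.90 | 0.039 | 0.043 |

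**Step 3: the other named tests.** At ICC 0.05 to 0.10 with s = 0, the simulated Wilcoxon error is 0.085 to 0.128. For chi-square (the simulated outcome cut at its mean) it is 0.089 to 0.116, against 0.058 at ICC = 0.

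**Step 4: tests on centre means.** In the same simulations with s = 0, a t-test on the six centre means rejects in 0.048 to 0.050 of trials at ICC 0.01 to 0.10, and a paired t-test on the three pair differences in 0.048 to 0.050. Degrees of freedom and two-sided 5 % critical values:
- individuals: 48 − 2 = 46, t = 2.01
- centres, pairs broken: 6 − 2 = 4, t = 2.78
- centres, pairs kept: 3 − 1 = 2, t = 4.30

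**The case against.** **The plan does not ignore clustering.** It commits to controlling for it without conditions. This is a journal article: the figure holding the analytic plan is not reproduced in the text at hand, and the choice of model can fairly be left to a fuller analysis plan. This stands in part. A reader might infer that clustering will be disregarded, and the document does not support that. But the article does more than leave detail out: it names tests and a significance rule, and these do not fit the promise made in the same paragraph.

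**The named tests are not wrong in themselves.** A two-sample t-test on six centre means is valid. This stands; the fault lies in applying the tests to individuals. The wording, which compares mothers with mothers and proportions in two groups, points to that use.

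**The size is uncertain.** This stands. The ICC is assumed, the excess is small at 0.01 to 0.02, and effective pairing could remove it. Nothing in the document shows how effective the pairing was.

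**The wording about mothers being randomised is merely loose.** Probably so, since two other places are clear. It is still worth correcting, because it invites an individual-level analysis.

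**Conclusion.** The point holds as a contradiction within the primary analysis section: a promise to control for clustering beside individual-level tests that cannot do so. It covers the continuous primary outcomes and exclusive breastfeeding at 6 months, and carries over to the secondary outcomes. For 8 infants per centre, the t-test's error at nominal 0.05 is about 0.06 to 0.13 over assumed ICCs of 0.01 to 0.10 if pairing removes no between-centre variance. At ICC 0.05 to 0.10 it is about 0.07 to 0.09 if pairing removes half, and not inflated if it removes all.

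Some stronger readings are tempting but not supported:
- *Dropping the pairs makes the p-values too optimistic.* The excess comes from ignored clustering; ignoring the pairing alone tends to be conservative, as the last two rows of the table show.
- *Adjustment depends on a preliminary test of clustering.* The text says the effects are being evaluated and will be controlled for; it states no such condition.
- *Every primary comparison is affected.* No test is named for the risk of stopping exclusive breastfeeding.
- *Planned confidence intervals will be too narrow.* The analysis sections plan p-values and mention no intervals.

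**What to change.** In the primary analysis section, and through it the secondary one, replace the individual-level tests with an analysis that has the centre as the unit of inference. Two forms would do:
- a comparison of centre-level summaries (means or proportions); or
- a mixed model with a random centre effect and a small-sample degrees-of-freedom correction, Kenward-Roger being one choice.

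State in advance whether pairs are kept (2 df) or broken (4 df). Apply the adjustment whatever the estimated clustering, and report the ICC for each outcome. When a method is named for stopping exclusive breastfeeding, let it follow the same rule. Reword the Participants section to say that centres were randomised and mothers enrolled. Rest conclusions on estimates with their uncertainty rather than on p ≤ 0.05.

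The cost is a change of wording and a little programming; data collection does not change. The real price is precision: with six centres, uncertainty will be wider and significance harder to reach. That reflects the number of centres randomised and is not created by the corrected analysis.

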Understanding the context in which obesogenic behaviors occur, helping parents of very young children to establish positive behaviors, and linking families to community resources could prevent the development of obesity in young children. These goals are the foundation of an intervention called the *Early Childhood Obesity Prevention Program (ECHO): Building Healthier Families and Communities.* ECHO is a randomized, controlled trial designed to examine the efficacy at 12 months of a home visitation program that engages mothers as agents of change to modify their own behavior and their infant’s behavior through education and skill building in the areas of nutrition, physical activity, and wellness, and then “echoes” her training with linkages to neighborhood programs (e.g., coupons to purchase fruits and vegetables at grocery stores and farmer’s markets, parenting classes at Family Centers, neighborhood cooking classes). ECHO recruits pregnant women and new mothers who have agreed to participate in NFN’s home visitation program and provides them with an enhanced curriculum that increases maternal skills in goal-setting, problem-solving, and stimulus control to target four specific infant-related behaviors (breastfeeding, SSB/juice consumption, introduction of solids, television/screen time and infant routines and cues around sleep and hunger and satiety) and follows the mother-infant dyad until the infant is 12 months of age. The program also provides education and linkages to community resources to improve the mother’s health, nutrition and physical activity. The study’s focus on newborns and mothers as agents of change adds to the small literature on obesity prevention in this critical developmental window.

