We hypothesized that at 6 and 12 months, as compared to NFN infants, NFN+ infants would have been breastfed longer and more often exclusively, would drink less sugar-sweetened beverages/juice, would have begun to ingest solids at an older age, and would sleep more hours/day, have more established sleep/wake routines, greater soothability and have fewer hours of television viewing/day. Secondary hypotheses of the study included that at 6 and 12 months, as compared to NFN families, NFN+ families would purchase, cook and serve more fruits and vegetables, demonstrate greater utilization of BFF Centers and community resources, and NFN+ infants would be less likely to have a weight for length greater than the 85^th^ percentile. The study protocol was approved by the Institutional Review Board at Connecticut Children’s Medical Center, was sponsored by the Hartford Childhood Wellness Alliance, and was funded by the National Institutes of Health (NICHD R21 HD073966-A01).

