##### Intervention strategies

Activities within each intervention strategy module take ~10-15 min of the scheduled 60–90 min home visit and are delivered at different visits. Each targeted behavior is addressed in a series of interactive modules that can be divided into multiple 15-min segments. For example, the Sugar Sweetened Beverage Module has four “messages” linked to four activities. Message 1 stresses no juice in the first 6 months of life and comes with a bib that says “No Sugar drinks for me, I am sweet enough.” Message 2 teaches mothers to buy only 100 % fruit juice. Message 3 educates mothers about the sugar content of 100 % fruit juice and Message 4 stresses limiting juice consumption to less than 6 ounces a day from 6 months to 7 years of age. The messages build upon each other but can be delivered separately or together and in any order. NFN+ mothers are trained to recognize hunger and satiety cues in their infant and to establish sleep routines. Mothers are also taught how to use “Tummy Time” to enhance infant activity and development and how to avoid television viewing. In addition, mothers who are bottle feeding learn proper formula dilution, storage, and how to use hunger and satiety cues regardless of the milk volume consumed. The messages in each intervention module are described in Table 3.

**Table 3 Tab3:** Intervention modules and messages

Intervention module	Intervention messages	Intervention activities/Components
Feeding My Baby	1. Breast milk is best	-Picture of mom breastfeeding infant
	2. Breast milk is the only food a baby needs until 6 months	-3 reasons to breastfeed
		-Importance/Confidence rulers
	3. If formula feeding, mix formula correctly	-Goal setting tool
		-Steps to achieving goal
		-Barriers/Problem solving
		-Community resources to support activity: Heritage and Pride program
		-Self-monitoring calendar
		-Progress assessment
Juice/Sugar sweetened beverages	1. No juice or SSB before 6 months of age	-Picture of baby wearing “No sugar drinks for me” bib
	2. Serve only 100% juice	-Education around messages
	3. Sugar in 100% juice	-How to read a label to determine sugar content and addition
	4. No more than 4-6 oz juice/day	-Measuring cup, 6 oz sippy cup, bib,toothbrush
		-Importance/Confidence rulers
		-Goal setting tool
		-Steps to achieving goal
		-Barriers/Problem solving
		-Community resources to support activity: Cooking Matters, Shopping Matters
		-Self-monitoring calendar
		-Progress assessment

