Little Tummy	1. Delay introduction of solids to 6 months	-Picture of baby (baby’s tummy)
	2. Do not add cereal to the bottle	-Education around messages
	3. How to introduce solids	-Measuring spoons
	4. What are the first solids	-Food card “quiz”
	5. Portion sizes	-Importance/Confidence rulers
		-Goal setting tool
		-Steps to achieving goal
		-Barriers/Problem solving
		-Community resources to support activity: WIC, Fruits and vegetable coupons
		-Self-monitoring calendar
		-Progress assessment
Screen Time	1. No TV/screen time under 2 years	-Picture of mother and infant looking at book, listening to music
	2. Remove TV from bedroom	-Education around message
		-Paper and crayons to make No TV sign
		-Importance/Confidence rulers
		-Goal setting tool
		-Steps to achieving goal
		-Barriers/Problem solving
		-Community resources to support activity: Brighter Future Family Center activities
		-Self-monitoring calendar
		-Progress assessment
Establishing Routines		
A. Rock-a-bye Baby	1. Infant sleep duration	-Picture of baby sleeping
	2. Create a healthy bedtime routine	-Education around messages
		-Sleep sack
		-Importance/Confidence rulers
		-Goal setting tool
		-Steps to achieving goal
		-Barriers/Problem solving
		-Community resources to support activity: Parenting support groups
		-Self-monitoring calendar
		-Progress assessment
B. Tummy Time	1. Use tummy time to play	-Picture of baby engaging in tummy time
		-Education around benefits of tummy time for baby and mother
		-Importance/Confidence rulers
		-Playmat
		-Goal setting tool
		-Steps to achieving goal
		-Barriers/Problem solving
		-Community resources to support activity: Parenting support group
		-Self-monitoring calendar
		-Progress assessment
C. Calm Baby	1. Techniques to soothe and calm baby instead of feeding	-Picture of mother holding baby
		-Education on hunger and satiety cues; strategies to calm baby
	2. Taking care of mother when infant is crying	-Importance/Confidence rulers
		-Goal setting tool
		-Steps to achieving goal
		-Barriers/Problem solving
		-Community resources to support activity: Parenting support group
		-Self-monitoring calendar
		-Progress assessment
Healthy Mom, Healthy Baby	1. Eat 5 servings of fruits and vegetables daily	-Picture of mother
		-Education about diet and physical activity; activity with her baby
	2. Get 10,000 steps a day	-Pedometer, Fruit and Vegetable coupons
	3. Be physically active 30 minutes/day 5 days/week	-Importance/Confidence rulers

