### Evaluation plan

Assessments will occur at birth and when the infant is 6 and 12 months. The Family Wellness Plan book is collected at 6 and 12 months and copied and returned to the family. Primary outcomes will be the child’s targeted behaviors at 12 months (i.e., extent and duration of breastfeeding, SSB consumption, timing of introduction of solids, sleep duration and soothability and television viewing) (Fig. 3). Assessed process variables include changes in mothers’ knowledge about dietary recommendations, intentions to make these changes, and self-efficacy to make healthy choices. Six month intermediary variables include changes in the home food environment and mothers’ shopping and cooking practices, child feeding styles, maternal stress, positive parenting practices, and community resource utilization. The RE-AIM analytic framework will be used [72, 73]. For RE-AIM, Reach will be explored by determining the percent of mothers/infants who were excluded and the reasons for exclusion, the percent of eligible mothers/infants who participated, and reasons for dropping out. Effectiveness will be evaluated by comparing differences in maternal behaviors at 6 months between control and intervention mothers and short-term attrition. For Adoption, intervention use (number of doses of each intervention and number of intervention types rendered) and NFN+ worker satisfaction and intention to use the intervention after study’s end will be evaluated. Implementation will be evaluated using the number of completed home visits and the association between these indicators and maternal behaviors. Maintenance will be assessed by examining child behaviors and weight for length *z*-scores at 12 months.

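### The analysis of stopping exclusive breastfeeding has no 6-month limit, so stops that follow the program's own teaching count as failures and dilute the estimated effect

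*Protocol article*

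**What the plan says.** The protocol article plans two analyses of exclusive breastfeeding under Statistical analysis plan for primary outcomes. The first has a fixed time point: "Chi square analysis will be used to compare the proportions of exclusive breastfeeding at 6 months in the two groups". The second follows at once, opens with the word *Similarly*, and has no time limit: "we will determine if the intervention decreases the risk that infants would stop exclusive breastfeeding at any time considered in the study".

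The study period is 12 months. The Background says that the program "follows the mother-infant dyad until the infant is 12 months of age". The Evaluation plan says "Assessments will occur at birth and when the infant is 6 and 12 months" and "Primary outcomes will be the child’s targeted behaviors at 12 months", and lists extent and duration of breastfeeding among those behaviors. The hypothesis in Overview and hypotheses is that "at 6 and 12 months, as compared to NFN infants, NFN+ infants would have been breastfed longer and more often exclusively".

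The program's own target is shorter. In Table 3 the Feeding My Baby module carries the message "Breast milk is the only food a baby needs until 6 months". The Little Tummy module carries "Delay introduction of solids to 6 months", followed by messages on how to introduce solids and which come first. The Family wellness plan section sets no juice before 6 months and a capped daily amount for the next 6 months.

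**The concern.** Exclusivity is named in the primary outcome measure. A mother who follows every module gives breast milk alone until about 6 months and then starts solids. Starting on that schedule is success on the solids outcome, but in the open-ended analysis it is an event of the kind the intervention is meant to prevent. Nothing in the article ends or censors this outcome at 6 months.

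Once infants in both arms move to solids on a similar schedule, the period after 6 months says nothing about whether the program worked. It only adds events that make the arms look alike. At stake is a bias toward no effect, and some loss of power, in a trial with 49 eligible dyads.

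**Working it through.** **Plan's own figure.** There is none for exclusivity. The sample-size paragraph concerns SSB/juice and/or solid food under 6 months. It is used here only for arm size: 60 × (1 − 0.20) = 48, or 24 per arm.

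**Passages side by side.**

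| Infant age | Program teaches | A stop is |
|---|---|---|
| Birth to 6 months | Breast milk only; no solids, no juice | An event, and a departure from the program |
| 6 to 12 months | How to introduce solids; capped juice | An event, but consistent with the program |

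This assumes that solids or juice end exclusivity, which fits the Feeding My Baby message. The article gives no definition.

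**Assumed rates.** Let pC and pN be the proportions exclusive at 26 weeks in control and NFN+. One anchor is available: the Background reports 65% of US infants on solids by 6 months, so at most 100 − 65 = 35% can be exclusive then. Formula and juice also end exclusivity, so the true control rate may be well below 35%.

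**Where the late stops fall.** If every infant still exclusive at 26 weeks stops before 12 months, the NFN+ share of late stops is pN/(pC + pN):
- 5% vs 20%: 20/25 = 80%
- 20% vs 50%: 50/70 = 71%
- 35% vs 65%: 65/100 = 65%

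**Hazard ratio.** With a constant stopping rate to week 26, the weekly rate is −ln(p)/26, so the ratio up to week 26 is ln(pN)/ln(pC):
- ln 0.20/ln 0.05 = 1.609/2.996 = 0.54
- ln 0.50/ln 0.20 = 0.693/1.609 = 0.43
- ln 0.65/ln 0.35 = 0.431/1.050 = 0.41

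After week 26 the infants still exclusive are assumed to start solids over the next few weeks, alike in both arms, so the ratio in that period is 1. A single ratio over the whole study averages the two periods. Simulated estimates, whose 26-week values agree with the formula to within about 0.02:

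| Exclusive at 26 weeks, control vs NFN+ | Ends at 26 weeks | Whole study |
|---|---|---|
| 5% vs 20% | 0.52 | 0.55 |
| 10% vs 20% | 0.71 | 0.74 |
| 10% vs 30% | 0.51 | 0.58 |
| 20% vs 50% | 0.44 | 0.58 |
| 35% vs 65% | 0.40 | 0.63 |

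The spread of late stops matters little, because the estimate depends on the order of events. With solids started over 8 weeks, the shift was 0.45 to 0.59 (20% vs 50%) and 0.42 to 0.65 (35% vs 65%).

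**Power.** Simulated with 24 per arm, two-sided 0.05, late stops over weeks 26 to 34:

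| Exclusive at 26 weeks | Log-rank to 6 months | Log-rank to 12 months | Loss (points) | Chi-square at 6 months |
|---|---|---|---|---|
| 10% vs 40% | 0.80 | 0.73 | 7 | 0.72 |
| 20% vs 50% | 0.64 | 0.53 | 11 | 0.61 |
| 30% vs 60% | 0.59 | 0.43 | 16 | 0.59 |
| 20% vs 40% | 0.37 | 0.31 | 6 | 0.33 |

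The simulation ignores clustering by neighborhood, so it serves to compare the two windows, not to state the trial's power.

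**Cumulative risk.** If the sentence means the proportion who have stopped by 12 months, and all infants have had solids by then, the comparison is 100% against 100% whatever the program achieved. This follows directly from the assumption.

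**The case against.** The strongest reply is that the program's target window is already tested: the chi-square comparison is fixed at 6 months. That stands. A reader might infer that the trial cannot detect an effect on exclusivity; the documents do not support this.

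Second, risk of stopping at any time reads naturally as a hazard. In a time-to-event analysis an infant who stops at week 27 still contributes a long, favorable time compared with one who stops at week 8, so differences before 6 months are kept. That also stands: the result is diluted, not void, and every whole-study hazard ratio above still favors NFN+. The wholly uninformative comparison arises only under the cumulative-risk reading, which the word *Similarly* after a chi-square sentence leaves open but does not establish.

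Third, the dilution is small when few infants are exclusive at 6 months, and the documents give no rates. That is correct, and it is why a range is shown.

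Two further inferences are tempting but unsupported. One is that the plan compares proportions exclusive at 12 months, near 0% in each arm: no section states such a test, and the hypothesis can be read as feeding history up to the visit. The other is that the 6-month chi-square is itself distorted by visits held after the 6-month birthday: nothing says that status is read as current feeding on a late visit date, and such details belong to the full protocol.

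What the reply does not remove is that the open-ended analysis is a stated rule for a component of the primary outcome, and that it counts program-consistent stops as failures.

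**Conclusion.** The point holds for one analysis. The risk-of-stopping analysis runs past the age at which the program itself teaches mothers to introduce solids, and this biases it toward no effect. The shift in the hazard ratio ranges from about 0.03 (0.52 to 0.55 at 5% vs 20%) to 0.23 (0.40 to 0.63 at 35% vs 65%). With 24 per arm the longer window costs about 6 to 16 points of power in the four scenarios run, and little where few infants are exclusive at 6 months. These figures rest on assumed exclusivity rates, a constant stopping rate to 26 weeks, the same timing of solids in both arms thereafter, and solids ending exclusivity. The 6-month chi-square test is sound, so this is a worthwhile correction to one stated rule and not a fault that undermines the trial.

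**What to change.** Define this outcome as time from birth to the end of exclusive breastfeeding, censor it at 6 months of age, and name a time-to-event method, with neighborhood clustering handled as the plan already intends. In Overview and hypotheses, word the exclusivity part as exclusivity up to 6 months, and keep duration of any breastfeeding as the comparison to 12 months. Leave the 6-month chi-square test as it is.

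The cost is wording. Ages at introduction of SSB/juice and of solids are already outcomes; the sponsor should confirm that the feeding questionnaires also record age at first formula. The downside is that no statement about exclusivity can be made beyond 6 months. Only the measurement window changes; nothing in the program's teaching needs to.
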